# Investigating the effect of an online enhanced care program on the emotional and physical wellbeing of patients discharged from hospital with acute decompensated heart failure: Study protocol for a randomised controlled trial: Enhanced care program for heart failure

**DOI:** 10.1177/20552076241256503

**Published:** 2024-05-28

**Keywords:** (MeSH terms): heart failure, depression, quality of life, internet-based intervention, randomised controlled trial

## Abstract

**Objective:**

Depression is highly prevalent and associated with increased hospitalisations and mortality among patients with heart failure (HF). This study will evaluate the effectiveness and cost-effectiveness of an online wellbeing program for patients discharged from hospital with acute decompensated heart failure (ADHF) in (i) improving emotional and physical wellbeing, and (ii) decreasing healthcare utilisation.

**Methods:**

Two-arm randomised controlled trial. Eligible patients with ADHF will be recruited pre-discharge from two hospitals. Five hundred and seventy participants will be randomised to receive the intervention (online enhanced care program for HF: ‘Enhanced HF Care’) or usual care. Enhanced HF Care includes health education (11 micro-learning modules) and monitoring of depression and clinical outcomes via fortnightly/monthly surveys for 6 months, with participants offered tailored advice via video email and SMS. Cardiac nurses track real-time patient data from a dashboard and receive automated email alerts when patients report medium- or high-risk levels of depression or clinical symptoms, to action where needed. General practitioners also receive automated alerts if patients report medium- or high-risk survey responses and are encouraged to schedule a patient consultation.

**Results:**

Sixty-five participants enrolled to-date. Co-primary outcomes (‘Minnesota Living with Heart Failure Questionnaire’ Emotional and Physical subscales) and healthcare utilisation (secondary outcome) at 1- and 6-month post-recruitment will be compared between treatment arms using linear mixed effects regression models.

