### Control

The usual care (control) group will receive standard care with involvement from cardiology and allied health teams which may differ by site. This includes an initial call within 2 weeks post-hospital discharge to educate and assess patients in regard to their understanding of their condition and treatment, a medication reconciliation and symptom management. Patients are recommended to have a follow-up appointment with their GP 1-week post-discharge and encouraged to formulate an action plan, and an appointment 1 month later with their cardiologist. Further support is offered in relation to exercise, lifestyle modification and palliative care depending on the patient's condition and prognosis. One- and 6-monthly data collection will obtain post-discharge care details including the use of health services.

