^ The co-primary outcome variables will be compared between treatment arms at 6-month post-recruitment. Using the physical and emotional domains of the MLHFQ as the co-primary outcome measures avoids contamination associated with using the same measure for evaluating clinical progress for intervention participants.

*Secondary outcomes:* Healthcare utilisation. Unplanned hospital readmissions and hospital emergency department presentations. Measured with data from the medical records and via patient self-report survey.

*Cost-effectiveness/Utility Analysis:* Medical Record Number data will be used to attribute individual patient costs based on hospital utilisation. A medical record audit will be conducted for each consenting patient via routinely collected health service records via the Medical Record Number. The following information will be collected via records audit: diagnoses; treatment received; whether the patient has been prescribed common pharmacological treatments for HF; details of the medication regimen; and whether the patient has been referred to a rehabilitation program. The follow-up surveys will also obtain information not available from hospital records, with additional service use captured using a modified version of the Client Services Receipt Inventory^
36
^ at 1- and 6-month follow-up, including utilisation of primary care, allied health and other community health services and information to estimate productivity losses and time off work.

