### Sample size and statistical analyses

*Sample size:* The power calculation was based on a previous study involving roughly 1200 patients. This study assessed changes in MLHFQ^
34
^ sensitivity and the minimum clinically important differences. It reported standard deviations of 7.2 (emotional domain) and 9.5 (physical domain) points, and a 0.5 correlation between baseline and follow-up data across both domains.

Anticipating a 30% drop-out rate by the 6-month follow-up, a baseline sample of 285 participants per group will provide 80% power to detect a clinically significant difference of 1.75 points in the MLHFQ emotional domain and 3.5 points in the physical domain after 6 months, while maintaining an overall type 1 error rate of 5%.

The recruitment phase is projected to span 18 months, based on the volume of patients and expected consent rate. With the participating hospitals treating approximately 540 ADHF patients annually, the proposed sample size is feasible*.*

*Statistical analysis:* The primary analysis population will be the intention to treat, defined as all randomised participants. The co-primary outcome variables will be compared between treatment arms using separate linear mixed effects regression models. The models will include: fixed categorical effects for time and treatment group, baseline value of the outcome variable, and their interaction. Stratification variables will be included as fixed effects. The model will account for serial correlations from the repeated measures on the same individuals. Least squared mean differences will be presented, with 95% confidence intervals and *p*-values. Assuming that missing outcomes are random would be unrealistic in this study due to the high death rate. Instead, we will address missing data by assuming it is not randomly missing, using pattern mixture models. These models hypothesise differences in mean outcomes between missing and non-missing data. By adjusting this parameter across a plausible range (tipping point method), we can test how much our conclusions rely on this assumption. To maintain the cumulative probability of a type 1 error at 5%, we will test each outcome in a hierarchical manner. We will only proceed to the second outcome if the hypothesis test for the first one yields a *p*-value less than .05. Testing will commence with the emotional domain, and then proceed to the physical domain.

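### The abstract assigns readmissions and emergency presentations to a linear mixed model with no stated allowance for time at risk, and the Methods name no model for them

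*Protocol article*

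**What the plan says.** - Abstract, Results: after naming the two MLHFQ subscales as co-primary outcomes, the same sentence adds that "healthcare utilisation (secondary outcome) at 1- and 6-month post-recruitment will be compared between treatment arms using linear mixed effects regression models".
- Data collection, Secondary outcomes: utilisation is "Unplanned hospital readmissions and hospital emergency department presentations", and it is "Measured with data from the medical records and via patient self-report survey".
- Control: "One- and 6-monthly data collection will obtain post-discharge care details including the use of health services". Whether the 6-month figure covers the time since the 1-month survey or the whole six months is not stated.
- Sample size and statistical analyses: "The co-primary outcome variables will be compared between treatment arms using separate linear mixed effects regression models". The terms listed are "fixed categorical effects for time and treatment group, baseline value of the outcome variable, and their interaction", plus stratification variables. On covariance the text says "The model will account for serial correlations from the repeated measures on the same individuals". On deaths it says "Assuming that missing outcomes are random would be unrealistic in this study due to the high death rate". No model for utilisation appears in this section.

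**The concern.** Utilisation is the only listed secondary outcome, and lower utilisation is part of the stated hypotheses. The abstract sentence is the only place where the document says how it will be compared between arms, and it names a model without leaving the matter open.

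That model was built for a questionnaire score measured at two visits. Readmissions and emergency presentations accumulate while a patient is alive and under observation. A linear model for the mean count, with no exposure term, treats a patient who died in week 3 without readmission like one who lived six months without readmission. If mortality differs between arms, the comparison mixes the event rate with survival: a programme that reduced deaths would lose some of its apparent benefit on readmissions, and one with more deaths would gain some.

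The planned tipping-point handling of missing MLHFQ scores does not solve this, because a count cut short by death is not a missing questionnaire.

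**Working it through.** **Inputs.** From the protocol: 285 per group, collection at 1 and 6 months, and a death rate called high without a figure. Event rates, between-patient variation and mortality are not given, so all of them below are assumptions. The protocol's only sample-size figure concerns the MLHFQ and is not at issue: 7.2 × √(1 − 0.5²) = 6.24 gives 200 per group for 1.75 points, and 200/0.7 = 286 against the stated 285.

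**1. Time at risk.** With constant mortality and a proportion q dead by 0.5 years, mean time alive is 0.5 × q / (−ln(1 − q)).
- q = 0.10: 0.05 / 0.1054 = 0.475 years.
- q = 0.20: 0.10 / 0.2231 = 0.448 years.

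At 1 event per person-year these are also the mean counts. The ratio is 0.448/0.475 = 0.94, about 6% fewer events in the arm with more deaths although the rates while alive are equal. No choice of covariance structure changes this.

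Against sampling error: with mean about 0.46 and gamma frailty variance 1, the count variance is about 0.46 + 0.46² = 0.67, so SE = √(2 × 0.67/285) = 0.069. The shift of 0.027 is about 0.4 SE, which moves rejection from 5% to about 7%.

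A simulation with higher rates (0.25 events per month in month 1, 0.12 per month after, frailty variance 1, 4000 replicates) gave, at 6 months with equal event rates:

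| Deaths, control v intervention | Linear, visit-specific variances | Person-time rate ratio |
|---|---|---|
| 20% v 10% | 7.9% | 5.4% |
| 30% v 15% | 12.0% | 5.2% |

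The first linear entry checks by hand: shift 0.038, SE = √(2 × 0.887/285) = 0.079, so 0.48 SE and about 7.7% rejection.

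**2. Variance over the two visits, equal deaths (15% per arm).** Rates ranged over 0.10–0.40 events per month in month 1 and 0.05–0.20 after, with frailty variance 0.5–2.
- Visit-specific variances: type I error 4.2–5.3%.
- One residual variance for both visits: 0.2–0.9% at 1 month and 10.0–12.2% at 6 months (12.7% if the 6-month count is cumulative). The mechanism is simple. With frailty variance 1 and the middle rates, the variances were 0.309 and 0.885, pooled 0.597. At 6 months the effective critical value is 1.96 × √(0.597/0.885) = 1.61, a two-sided 10.7%. At 1 month it is 1.96 × √(0.597/0.309) = 2.72, or 0.6%.
- Person-time rate ratio: 5.0–5.4%.

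**3. Power.** At a true rate ratio of 0.75 with equal deaths, the same middle-rate scenario gave 47% for the linear contrast with visit-specific variances and 58% for the rate ratio. These are not like for like: the linear figure uses events after month 1 only, the rate ratio uses all six months. Putting the linear contrast on six months: difference 0.061 + 0.136 = 0.197; variance about 1.477 × 0.746/0.885 = 1.245; SE = √(2 × 1.245/285) = 0.0935; 0.197/0.0935 = 2.11, so power is about 56%. A separate comparison at rate ratio 0.7 found 61% for both methods. With equal deaths there is therefore little or no power loss on a common window.

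With deaths of 20% v 10% (control v intervention) the simulated figures were 29% and 60%. On six months the linear difference is 0.059 + 0.104 = 0.163, the variance about 1.477 × 0.741/0.885 = 1.237, and 0.163/0.0932 = 1.75, giving about 42% against 60%. That loss is real and comes from the missing time at risk.

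**The case against.** The strongest reply is that one abstract sentence compresses several outcomes. The Methods restrict the linear model to the co-primaries, and a fuller analysis plan may name a count model. If the article were merely silent, that would answer the point. It is not silent: a model is named, and nothing in the Methods corrects it. What stands of this reply is that the defect may lie only in the abstract's wording, which makes the repair easier but still necessary.

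Second, a reader might infer that the intervals must be far too wide at 1 month and too narrow at 6 months. The documents do not support that. It requires one residual variance common to both visits, and the Methods mention only serial correlation, neither stating nor excluding a common variance. With visit-specific variances and equal deaths the linear contrast of mean counts is close to nominal at this sample size.

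Third, the bias from deaths depends on a mortality difference that nobody has observed. The 6% requires mortality to double between arms and amounts to about 0.4 SE. This is fair: the effect is modest unless mortality differs widely.

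Some further readings also go beyond the text. No event rates are given, so calling the counts sparse is an inference. A 5-month second window is one reading of the collection times, and a cumulative count is another. The baseline-value covariate is specified for the co-primaries, so its poor fit to readmissions is not a stated error. Using records and self-report together is not in itself a defect.

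**Conclusion.** The point holds in limited form. The abstract names a linear mixed model for event data, the Methods name none, and the model as described has no term for time at risk although the same section cites a high death rate.

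The sure consequence is that unequal deaths distort the comparison. Under the assumptions shown this is about 6% in the mean count at 20% against 10% mortality, with rejection of about 7–8% instead of 5%, rising to 12% at 30% against 15%. A true reduction is correspondingly harder to detect when the intervention also lowers mortality.

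The larger type I error, under 1% at 1 month and about 10–13% at 6 months, is conditional on a common residual variance. With equal deaths and visit-specific variances, type I error is about 5%, and the apparent power gap largely reflects different windows. All sizes rest on assumed rates. The issue concerns the secondary outcome only; the hierarchical tests of the MLHFQ domains and the sample size are untouched.

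**What to change.** Replace the abstract statement and add to the statistical analysis paragraph, for example: unplanned readmissions and emergency department presentations will each be analysed by negative binomial regression (or Poisson regression with robust variance), with log of time alive and followed as offset and recruitment site as covariate, over windows defined in advance; rate ratios with 95% confidence intervals will be reported, with the number of deaths by arm beside them.

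Add a sensitivity analysis that treats death as a terminal event. The offset model assumes that death is independent of a patient's propensity for events, and so did the simulations above, so the offset alone does not settle the matter of deaths.

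The cost is small: a different standard model on data already being collected, plus dates of death or last follow-up to compute time at risk. The Trial status section reports 65 enrolled of a planned 570 at 5 April 2024, so the wording can be settled well before analysis.

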**Conclusions:**

This study has the potential to reduce the burden of depression for patients with HF by prioritising urgent mental health needs and clinical symptoms while simultaneously empowering patients with self-care knowledge.

**Trial registration:**

The trial was prospectively registered via the Australian New Zealand Clinical Trials Registry: ACTRN12622001289707. Issue date: 4 October 2022.

## Introduction

Heart failure (HF) is a debilitating and economically burdensome condition,^
1
^ estimated to impact over 64 million people globally,^
2
^ with costly hospitalisations and high comorbidity and mortality.^
3
^ Acute decompensated heart failure (ADHF), the worsening of symptoms of HF, is a frequent cause of hospitalization^
4
^ and patients experience poor outcomes. In addition to significant mortality rates, there have also been several gaps demonstrated in patient care for emotional wellbeing.^5,6^ Almost 50% of patients with HF have depressive symptoms and approximately one-third have symptoms of anxiety.^
7
^ Depression has been associated with increased hospital utilisation, reduced health functioning and a higher risk of all-cause mortality.^
8
^ Given the interaction between emotional wellbeing and physical outcomes including disease progression,^
9
^ as well as the importance of patients’ mental health, there is a need for increased emotional support and information for patients with HF.

The post-diagnosis and post-discharge periods can be an overwhelming and anxious time for patients, and this anxiety is associated with reduced retention of information.^
10
^ Previous data also indicates that when patients with HF are experiencing depressive symptoms, these symptoms are unrecognised by providers in 50% of cases.^
11
^ Follow-up community care is typically nurse-led but varies in length and intensity. Innovative models are required for improving discharge support and community care, which harness existing community resources, such as general practitioners (GPs), and increases the probability of a care partnership between healthcare providers, patients, and their support persons.

Consistent focused post-discharge community support may offer significant opportunity to improve emotional and physical wellbeing of patients with HF. Secondary prevention including the identification and management of modifiable health risk factors, psychosocial care, education, and support for self-management is also important and guideline recommended.^
12
^ For example, preventive strategies such as exercise have been shown to have positive effects on cardiovascular disease,^
13
^ including patients with HF,^
14
^ and individuals with risk factors for cardiovascular disease, such as type 2 diabetes and obesity.^15,16^ Digital health interventions represent a potentially effective mechanism for helping patients with HF manage their emotional and physical wellbeing.^
17
^ Studies that have examined the effectiveness of digital health interventions to improve emotional outcomes for patients with HF or other cardiovascular diseases have predominantly focussed on mobile health interventions.^18,19^ A systematic review of smartphone interventions for comprehensive cardiac rehabilitation and HF rehabilitation and management found mHealth interventions feasible and effective in improving quality of life.^
18
^ However, findings are mixed, with Antypas et al. reporting no statistically significant difference for a mobile intervention in relation to secondary outcomes of anxiety and depression.^
20
^ Further, small sample sizes were reported. High-quality randomised controlled trials (RCTs) are needed to test whether digital health interventions can improve emotional wellbeing in patients with HF.

The Enhanced HF Care program, a digital health intervention, seeks to improve care coordination with a proactive approach to monitoring and managing emotional and physical wellbeing. The proposed program will achieve this through: (i) recognising the interaction between emotional and physical wellbeing; (ii) harnessing existing community resources, such as GPs; (iii) supporting patient empowerment through offering education and self-help strategies; (iv) providing a mechanism for tailored self-help and stepwise care; (v) using clinically derived algorithms to offer care recommendations; and (vi) increasing the probability of a care partnership between hospital providers, community health, the patient and their support persons.

*Aims:* To determine using a RCT among patients hospitalised with ADHF, the effectiveness and cost-effectiveness of a cardiovascular wellbeing program in (i) improving emotional and physical wellbeing (co-primary outcomes), and (ii) decreasing healthcare utilisation (secondary outcome).

*Hypotheses:* Relative to control participants, intervention participants will have: higher emotional and physical wellbeing scores (co-primary outcomes) 1- and 6-month post-recruitment; and attainment of this increase will be cost-effective, with intervention participants having lower health service utilisation.

## Methods

### Study design and setting

Prospective randomised open blinded end-point design.^
21
^ A two-arm RCT with participants randomly allocated to receive the intervention (an online enhanced community care program for HF: ‘Enhanced HF Care’) or usual care. Up to 570 patients will be recruited prior to discharge from two hospitals (one metropolitan and one rural) in the Hunter New England local health district. Located within New South Wales, Australia, this region covers more than 130,000 km^2^ and has a population of approximately 910,000. An estimated 55% of the population is in regional or rural areas. The trial was prospectively registered via the Australian New Zealand Clinical Trials Registry: ACTRN12622001289707. Issue date: 4 October 2022.

### Sample

#### Eligibility criteria

*Inclusion criteria:* Patients eligible to participate are those hospitalised with ADHF (including all ejection fraction classifications) being discharged from participating hospitals to home; aged 18 years or older; English speaking; with access to, and ability to utilise, a device with internet; and able to provide informed consent. In 2020, Australian data indicated that 78% of those aged 65 + years had used smartphones to access the internet in the past 6 months, with online activities (including telehealth) substantially increasing throughout the COVID-19 pandemic.^
22
^

*Exclusion criteria:* Ineligible patients are those without access to a device with internet, and who are unable to provide written informed consent.

#### Recruitment

Prior to hospital discharge, the cardiac research nurse will identify (via daily patient lists) and invite all potentially eligible patients to participate. The nurse will confirm eligibility, provide verbal and written study information and seek the patient's written informed consent to participate via an iPad. Patients will be informed that they do not have to make an immediate decision on participation and can consider the information materials, before deciding whether they would like to participate. If this is the case, the research nurse will visit the patient again in 24 h’ time to answer any questions they might have and seek their consent for participation. If the patient is discharged during this period, they will be unable to participate.

#### Randomisation

Immediately after providing informed consent to participate in the RCT, participants are asked to complete a baseline survey via an iPad. Upon survey completion, the patient will be randomised to either (i) usual care or the (ii) Enhanced HF Care intervention, using permuted blocks, stratified by recruitment site. The allocation sequence is generated by an independent statistician at the Clinical Research Design and IT and Statistical Support Unit of the Hunter Medical Research Institute, and the randomisation schedule is embedded in the patient baseline survey. Group allocation will be created with blocks of sizes two and four selected randomly.

*Blinding:* It is not possible to blind trial participants or cardiac nurses to allocation. Only intervention group participants will be given access to the online enhanced care program via unique link. Research nurses will be aware of trial allocation as they will be involved in supporting intervention group participants to access and use the intervention. Outcome assessors and data analysts will be blinded to allocation.^
21
^ While there is a small risk that the use of small block sizes could lead to subversion of the randomisation process, the permutation of the different blocks sizes, as well as the fact that the recruiting nurses are not aware of the blocks sizes, with the randomisation sequence performed externally by an independent statistician, will all in aide minimising this risk.

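### The article publishes block sizes of two and four mid-recruitment, so nurses' unawareness of them is no longer a safeguard; the root weakness is very small blocks with unblinded recruiters

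*Protocol article*

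**What the plan says.** The Randomisation section of the protocol article describes 1:1 allocation "using permuted blocks, stratified by recruitment site", with two sites, and gives the block sizes: "Group allocation will be created with blocks of sizes two and four selected randomly". The sequence comes from an independent statistician and is built into the baseline survey, so an allocation appears only after consent and completion of that survey.

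The Blinding paragraph of the same section acknowledges that "there is a small risk that the use of small block sizes could lead to subversion of the randomisation process". It offers three reasons why the risk is contained: the sizes vary, "the recruiting nurses are not aware of the blocks sizes", and the sequence is produced externally. It also says: "Research nurses will be aware of trial allocation as they will be involved in supporting intervention group participants".

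Under Recruitment, "the cardiac research nurse will identify (via daily patient lists) and invite all potentially eligible patients to participate". The same nurse confirms eligibility and seeks consent. The article is dated 28 May 2024, and Trial status reports 65 enrolled at 5 April 2024.

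**The concern.** One of the three reassurances depends on the block sizes being kept from the recruiters, yet the section that gives it prints them in an open publication while most of the randomisation is still to come.

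The other two reassurances do not fill the gap. External generation hides the list but does not prevent inference from allocations already seen. Varying the size helps little when the largest block is four, because once one arm leads by two at a site the next two allocations are fixed.

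The people placed to make that inference also choose whom to approach and when. If a nurse expects a particular arm next, the decision to invite a given patient now or later can depend on that expectation, perhaps without intent. The trial is open to participants and its co-primary outcomes are self-reported, so arms that differ at entry could distort the comparison.

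**Working it through.** The plan gives no figure for predictability and describes the risk only as small, so there is nothing to reproduce.

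**Inputs**
- Block sizes 2 and 4 (Randomisation). Selection probabilities are not stated; equal selection is assumed, with weights (size 2 : size 4) from 3:1 to 1:3 as the range.
- 1:1 allocation, from "a baseline sample of 285 participants per group" (Sample size and statistical analyses).
- One sequence at each of two sites. A length of 285 per site is assumed (570/2).
- The observer is assumed to see every earlier allocation at the site. The text supports awareness of allocation, but gives neither the number of nurses nor any sign that a tally is kept.

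**Step 1. How much remained.** 570 − 65 = 505, and 505/570 = 88.6%, as of 5 April 2024.

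**Step 2. Guessing without knowing the sizes.** Always choose the arm that is behind at the site, and toss a coin when the arms are level. Every completed block is balanced, so the running tally is enough. Expected correct guesses:
- Block of 2: 1/2 + 1 = 1.5 of 2.
- Block of 4: 1/2 + 2/3 + (1/3 × 1 + 2/3 × 1/2) + 1 = 2.833 of 4.
- Equal selection: (1.5 + 2.833)/(2 + 4) = 0.722.

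A simulated observer who knows the sizes and updates exact probabilities before each allocation also scores 0.722. Knowing the sizes does not raise the guess rate.

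**Step 3. What knowing the sizes adds.** It tells the observer when a guess is safe.
- *Certain.* A lead of two arises only when a block of 4 opens with the same arm twice, and its last two places are then fixed. With equal selection, 4/6 = 2/3 of participants are in blocks of 4, 1/3 of those blocks open that way, and half of their places are fixed: 2/3 × 1/3 × 1/2 = 0.111. At weights 3:1, 4/10 of participants are in blocks of 4: 0.4 × 1/6 = 0.067. At 1:3 it is 12/14 × 1/6 = 0.143. Simulation gives 0.110, with range 0.066 to 0.142.
- *Probability at least 0.80.* With equal selection, after the first allocation of a new block the other arm follows with probability 1/2 × 1 + 1/2 × 2/3 = 0.833, and any other unequal tally is at least as informative. So every unequal tally counts: 1 of 2 places in a block of 2, and 1 + 1/3 + 1 = 7/3 of 4 places in a block of 4, giving (1 + 7/3)/6 = 0.556. Simulated sequences of 285 give 0.553, and 0.446 to 0.553 over the selection weights.

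**Step 4. Larger blocks for contrast.** The same simulation with sizes 4, 6 and 8, equally likely and known to the observer. The lagging-arm rule again does equally well without the sizes (0.680).

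| Schedule | Guessed correctly | Certain | Probability ≥ 0.80 |
|---|---|---|---|
| 2 and 4, equal selection | 72% | 11% | 55% |
| 2 and 4, weights 3:1 to 1:3 | 71–73% | 7–14% | 45–55% |
| 4, 6 and 8, equal selection | 68% | 2% | 25% |

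**The case against.** The strongest reply is that publication changes little. A nurse who simply backs the lagging arm is right 72% of the time without reading the article. That stands. A reader might infer that disclosure is what lifts prediction from 50% to 72%, or that secrecy alone would bring it down. The arithmetic supports neither. Disclosure adds only knowledge of when a guess is certain or nearly so.

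Second, the protocol recognises the trade-off and lists three safeguards, and nothing shows that any recruiting nurse has read the article. This also stands in part: the statement that nurses are unaware has not been shown to be false. It has become something that the trial can neither ensure nor rely on.

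Third, there are limits on acting on a guess. Nurses work from daily lists and are to invite every potentially eligible patient, the eligibility criteria are short, and allocation cannot be looked up before consent and the baseline survey. A patient may take 24 hours to decide and is lost if discharged meanwhile. These limits narrow the opening without closing it, since whom to approach and when remains with the nurse.

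Fourth, the models adjust for baseline MLHFQ and site, so it would go too far to say that analysis can do nothing about selective recruitment. The adjustment covers those measured differences only.

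Finally, the percentages measure predictability under a full-tally assumption. They are not an estimate of bias in the MLHFQ difference.

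**Conclusion.** The point holds as a weakness in allocation concealment that should be corrected for the participants still to come. One stated safeguard cannot be relied on now that the sizes are public, and the deeper cause is blocks of at most four, stratified only by two sites, with recruiters who see allocations. If the sizes are equally likely and all earlier site allocations are seen, about 72% of allocations can be guessed with or without the sizes. With them, about 11% are certain and about 55% have probability 0.80 or more. If several nurses each see only part of a site's sequence, the figures would be lower.

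A reader might go further and conclude that the randomisation has been subverted or that the results will be biased. The documents support neither; they show an exposure in whom is approached and when.

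**What to change.** For participants still to be randomised, the independent statistician should load a new schedule, still stratified by site, with larger and varied block sizes that are not disclosed outside the statistics unit until recruitment ends. The protocol should then state only that block sizes vary, and should stop offering unawareness of the published sizes as a safeguard. Sizes of 4, 6 and 8 are used above for illustration; the actual choice should not be published. Both elements matter: larger blocks lower the guess rate and the certain share even if the sizes leak, while non-disclosure withholds knowledge of when a guess is safe. Neither removes predictability entirely, since about 68% can still be guessed in the illustration.

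The cost is one new schedule in the existing survey system and a short amendment. Existing allocations are untouched. The statistical price is a possible final imbalance of a few participants per site. With a largest block of 8 it is at most 8/2 = 4, plus at most 4/2 = 2 from a block left unfinished at the switch, against an assumed 285 or so per site.
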